#### Number of subjects for the aggregation of the N-of-1 trials

For aggregating the multiple N-of-1 trials, we used the average comfort of a lower limb amputee 7.2/10 (SD= 2.3, inter-patient variance of 5.3) found by Hafner Brian et al. [19] and, (because of lack of data on Unity) our clinical experience that the Unity system would increase comfort by 2/10 points. Based on the calculation proposed by Senn [27] (formula 3 and 4 in the study) to calculate the necessary number of subjects and wanting to detect a clinical difference of 2, with an alpha at 5% and a power at 80%, and assuming that the intra-patient variance is 2, 16.35 subjects are required. If patients stop the study, they can contribute to the analysis of each completed phase. Recruiting 20 patients will allow to satisfy the sample size even in case of early dropouts.

### Data management and independent committee

Each investigator will be responsible for ensuring data completeness. Data management will be handled centrally by the Clin Experts Company. The research in the investigational centers and management of subjects will comply with the Declaration of Helsinki and Good Clinical Practices. Each investigator will be monitored by telephone on a regular basis to keep informed about the progress of the trial, adverse events that occurred during the trial and possible recruitment difficulties. A study progress report will be drawn up every 30 days for the duration of the study. Clin Expert (RU) is responsible for study supervising data collection, auditing recruiting centers for regulatory procedures, for data completeness and supervision of investigators. No steering committee monitoring adverse effects is used because there is no particular risk for the participants (apart from possible lesser comfort). Conversely, an independent committee ([name], [name]) will check data and protocol integrity. Data statistical interpretation will be performed by a statistician blinded to the hypothesis of the study (JG).

### Ethics committee approval and dissemination of results

This protocol of the study (version 2) was approved by the French Committee for the Protection of Research Participants “CPP SUD MÉDITERRANÉE 1”, (i.e. official French Institutional Review Board) on July 20, 2020 (2020-A01309-30), and by the French Health Products Safety Agency (ANSM) on June 26, 2020 (2020-A01309-30). Prior to the start of the study , the High Authority of Health reviewed the methods, and approved the use of a multiple N-of-1 trail for determining the use (and reimbursement) of Unity. Data will be collected according to methodology (MR-001) issued by the French Data Protection Authority (the, "CNIL"). This methodology is used to simplify the authorization process for the processing of personal data in France and to enforce protection of personal data. Data collected will be collected on paper form (All important protocol modifications will be communicated to both CPP and ANSM, and then transmitted to each center after validation). ANSM and the French High Authority oh Health will be notified of the results and given access to raw data on request. Each participant will receive a personalized statistical analysis report of the effectiveness of the system. A paper of the results will be produced by the same authors, and 3 additional center investigators, without any third party or medical writer involved, apart from English correction.

### Statistical analysis

#### Statistical analysis of each patient’s N-of-1 trial

Effectiveness of the Unity system regarding SCS and daily secondary outcome measures will be tested by randomization test [20, 28], using the mean of each phase. Randomization allows reliable statistical analysis of auto correlated data (such as data from N-of-1 trials) and allows to extract a statistical effect for each participant separately. Missing data points will be managed by multiple imputation method. In case of a rescheduled transition visit, the real transition date and not the initially scheduled one will be used.

The secondary outcome measures assessed during visits in the rehabilitation center will be analyzed by NAP (Non Overlap of All pairs) [21, 22]. NAP is an estimate of the probability that a randomly selected point in Phase B shows an improvement over a randomly selected point in Phase A with θ=Pr(YB>YA)+0.5×Pr(YB=YA). Since NAP's interpretation of effect size according to Cohen's rules (d=3.464⁎(1√(1-NAP)/.5) has been shown to be inadequate, Parker's criteria will be used [21] (effect present but small if NA*P =* 0.5-.65; moderate effect: .66-.92; large effect: .93-1.0.). NAP [21] will also be applied to daily outcome measures, in addition to randomization tests, to obtain an effect sizes.

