### Design

After the inclusion visit, a prosthesis (with an Iceross Seal-In™ liner) equipped with an Össur-compatible foot and a Unity system will be manufactured for each included patient. Each center will have one single prosthetist, trained and qualified for the Unity system by the Össur company, who will manufacture all the prosthesis of the trial but will be independent of the team performing the study. Each patient will wear the new prosthesis with the Unity system connected for 28 days, before beginning the N-of-1 trial. This acclimation period is necessary to adjust the prosthesis and obtain a stability in patient’s daily activities.

The N-of-1 trial will then last 50 days for each patient, following a design with random alternation of Unity connection and disconnection of minimum 7 days periods. This minimum period has been decided in order to include a weekend in each period, as patient’s activity level is expected to be variable between weekdays and weekends. Randomization will be performed on R, SCDA (Single Case Data Analysis) plug-in package, by an off-center independent operator. The randomization will use a phase length ABAB randomization (i.e. allowing periods of unequal duration, which allows to interpret results with individual statistical significance) rather than block randomization commonly used in drug trials. “A” is for Unity system disconnected, and “B” for Unity system connected (see Fig. 1). However, because the patient has to come to the rehabilitation center at each phase change which would not allow the patient and the assessors to be blind to the next phase content, phases of a duration >14 days will be further randomized into two half-phases (of 7 days minimum), of the same content i.e. either connected or disconnected. A placebo visit between the two half-phases will allow to keep the blinding. The maximum phase duration obtained by ABAB randomization is 29 days, which will be further randomized to half-phases of minimum 7 days, meaning that the maximum duration of a half-phase is 22 days.

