### Sample size calculation

#### Power calculation for each N-of-1 trial (i.e. each patient)

One method for calculating power in a single N-of-1 trial (i.e. for a single patient) is calculating the number of possible randomization assignments [25, 26] which depends on the type of randomization, the number of phases and the number of measurements per phase. The greater the number of possible assignments, the greater the possibility of detecting a treatment effect that exceeds the threshold of significance of 0.05 if an effect exists. With 4 true phase transitions, with a minimum duration phase of 7 days, a maximum study duration of 50 days, and 1 measurement per day, the number of assignments generated by this design is therefore 2300, allowing a significance of up to *p =* 0.0004 for each patient, as calculated on R package for single-cases [17].

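### Multiple imputation is prescribed for the per-patient randomization test without the condition that keeps that test exact

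*Protocol article*

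**What the plan says.** In the protocol article, section Statistical analysis of each patient's N-of-1 trial, SCS and the daily secondary outcomes "will be tested by randomization test [20, 28], using the mean of each phase". The same paragraph continues: "Missing data points will be managed by multiple imputation method". The section on power for each N-of-1 trial sets "the threshold of significance of 0.05" and describes the series as one "with a minimum duration phase of 7 days, a maximum study duration of 50 days, and 1 measurement per day". It adds that "the number of assignments generated by this design is therefore 2300". Under Design, "The randomization will use a phase length ABAB randomization".

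The article does not say whether phase enters the imputation model, how results from several imputations are combined, whether the test is one- or two-sided, or what share of missing days is expected. The section on aggregation has the analyst blinded to phase allocation. Under Outcome measures, reminders, telephone calls and monthly charts of missing data are planned.

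**The concern.** The p-value compares the observed contrast with the contrasts that the same 50 scores would give under every other admissible schedule. This is exact because, under no effect, the scores are the same whichever schedule was drawn. A score imputed from a model that contains the actual phase breaks this link. It depends on the schedule drawn and copies that schedule's chance difference into the gaps. The actual schedule gets the full benefit of the copy, and schedules far from it do not.

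Putting phase in the model would be an ordinary choice, since imputation models usually include the variables to be analysed. Blinding the analyst does not rule it out, because a coded phase label can still enter.

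The individual verdicts are at stake. They bear on the comparison of responders with non-responders and on the personal report to each participant. The Discussion also suggests that funding could one day follow individual significance. The population conclusion rests on the Bayesian posterior and not on this test.

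**Working it through.** **Reference set.** Inputs from the article: 50 days, four phases (ABAB, A first), at least 7 days each. The number of schedules is C(50 − 4×7 + 3, 3) = C(25, 3) = (25×24×23)/6 = 2,300, as stated. The smallest p is 1/2,300 = 0.0004, as stated. The longest phase is 50 − 3×7 = 29 days, which agrees with Design. The text speaks of four transitions, whereas 2,300 belongs to four phases and so three transitions; this does not affect the present point.

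**Assumptions, because the article gives no figures.** Normal daily scores with AR(1) correlation 0, 0.3 or 0.6; days missing completely at random; 5% to 30% missing; one- and two-sided tests. Imputation is proper Bayesian normal with 10 imputations, held fixed while all 2,300 schedules are run. There were about 24,000 to 32,000 simulated patients per setting, so the Monte Carlo standard error at 0.05 is √(0.05×0.95/24,341) = 0.0014 or less.

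**Type I error at nominal 0.05, 20% of days missing, two-sided.** Ranges are over the three correlations and two forms of the phase-mean contrast.

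| Imputation model | How imputations are combined | Error |
|---|---|---|
| A/B phase in model | statistic averaged at every schedule | 0.090-0.102 |
| A/B phase in model | single completed set | 0.085-0.100 |
| A/B phase in model | median p | 0.061-0.084 |
| A/B phase in model | mean p | 0.035-0.065 |
| A/B phase in model | Rubin-type pooling of z | 0.029-0.050 |
| Four separate phases in model | statistic averaged | 0.085-0.094 |
| Phase not in model | statistic averaged | 0.047-0.053 |
| Phase not in model | single completed set | 0.048-0.051 |
| Phase not in model | median p | 0.029-0.037 |
| Phase not in model | mean p | 0.014-0.026 |

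One-sided, with A/B phase in the model, the averaged statistic gives 0.068-0.078 and mean p gives 0.034-0.054.

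**Dependence on the missing share** (A/B phase in model, averaged statistic, AR(1) 0.3, two-sided): 0.059 at 5%, 0.071 at 10%, 0.138 at 30%.

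**Observed days only,** with the missing-day pattern held fixed over all schedules: 0.047-0.051 for 5% to 30% missing, one- or two-sided.

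**Power** (20% missing, AR(1) 0.3, true shift of 1 within-patient SD, two-sided): full data 0.56; observed days 0.50; phase-free imputation with averaged statistic 0.49, single set 0.43, mean p 0.34.

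**Separate checks.** A second simulation, two-sided at 20% missing, gave 0.095-0.100 for phase in the model with averaged statistic, 0.043-0.052 for phase-free imputation with a single set or averaged statistic, 0.014-0.015 for phase-free with averaged p-values, and 0.042-0.049 for observed-day means. In one run where missingness differed by phase, observed-day means gave 0.046.

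**The case against.** The strongest reply is that the harm comes from choices the article does not make. It does not put phase in the imputation model, does not fix a pooling rule, and gives neither sidedness nor a missing rate. A journal article normally leaves such details to the full protocol or SAP. Phase-free imputation with an averaged statistic is exact and has power 0.49 against 0.50 for observed days, so a sound version of the stated plan exists. With phase in the model, mean p or Rubin-type pooling stays near or below the nominal level in most settings.

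Much of this stands. A reader might infer that multiple imputation as such invalidates the test, that false positives simply double, or that leaving phase out makes the test conservative. The documents support none of these. The doubling needs phase in the model, fixed imputed values, a two-sided test, an averaged statistic or single set, and about 20% missing. The conservatism of phase-free imputation comes from pooling p-values or z-scores and not from the imputation. Planned reminders and calls may also keep the missing share low.

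Two things remain. First, the article does more than leave a detail open: it names a missing-data method for a particular test, and that pairing is valid only under a condition it does not set. Second, the phase-in version with mean p is no safe default. It showed power of 0.56, but its error moves between 0.035 and 0.065 with the correlation and the statistic, so nothing guarantees its level.

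**Conclusion.** The point holds as a conditional weakness in the per-patient analysis that is cheap to remove. Depending on unstated choices, the prescribed pairing gives a two-sided error anywhere from about 1.5% to about 10% at 20% missing days. At 5% missing, the averaged statistic with phase in the model reaches only about 6%. Among the versions that hold the level, imputation brought no gain in power over observed days.

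These sizes rest on assumed missing rates, normal AR(1) scores and data missing completely at random. Missingness that depends on phase was checked in one run only, and exactness of the observed-day test is not guaranteed there. The point concerns individual p-values for SCS and the daily secondary outcomes. It does not touch the hierarchical Bayesian analysis, for which the article prescribes no imputation.

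**What to change.** For the randomization test, replace the imputation sentence with one to this effect: each phase mean is computed from the days observed; missing days stay missing in all 2,300 schedules; any schedule that leaves a phase with no observed day is excluded from the reference set. The p-value then uses the number of schedules that remain. If the actual schedule is itself excluded, no test is reported for that patient and outcome.

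If imputation is kept, state instead that the imputation model omits phase and that the statistic, not the p-value, is averaged over imputations at every schedule.

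The cost is one sentence plus the exclusion rule. The analysis becomes simpler, with no material loss of power against the valid imputation versions (0.50 against 0.49 or less in the setting above).

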**Patients-Reported Outcomes Measures (PROMs)**	
- 2 PROMs about indirect assessment of the stump volume variation:	
** 1.a** “How many times have you removed your prosthesis during the day (not counting the evening’s removal) to add compensation sheaths? “	0, 1, 2, 3, 4, >4,
** 1.b** “Did you have the fear at one (or more) moment(s) of the day, of losing your prosthesis, that it would come off by itself? “	VAS^a^: 0 = not at all 10 = yes a lot
- 2 PROMs on the limb-prosthesis fitting:	
** 2.a** “Do you feel in control of your prosthesis, as if the prosthesis is one with you?”	VAS^a^: 0 = not at all 10 = perfectly
** 2.b** “Do you feel pistoning movement of your prosthesis when walking (sensation of vertical movement of the prosthesis because of the stump when walking)?”	VAS^a^: 0 = not at all 10 = yes a lot
- Wearing time of the prosthesis	In hours
**At each phase change visit twice**^b^	

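### The NAP bands label the no-effect value 0.5 as a small effect, have no category for no effect or worsening, and leave the direction unstated for lower-is-better outcomes

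*Protocol article*

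**What the plan says.** The section on statistical analysis of each patient's N-of-1 trial describes NAP as the probability that "a randomly selected point in Phase B shows an improvement over a randomly selected point in Phase A" and writes it as "θ=Pr(YB>YA)+0.5×Pr(YB=YA" (closing bracket cut here). It then adopts published bands: "effect present but small if NA*P =* 0.5-.65; moderate effect: .66-.92; large effect: .93-1.0". There is no band below 0.5 and none called no effect.

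NAP has two uses. For visit outcomes it is the analysis: "The secondary outcome measures assessed during visits in the rehabilitation center will be analyzed by NAP". Table 3 lists these as the L-Test, 6-minute walk test, QUEST and ABC-S. For daily outcomes it is an addition: it "will also be applied to daily outcome measures, in addition to randomization tests, to obtain an effect sizes".

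Three daily items in Table 3 improve downwards: 1.a ("How many times have you removed your prosthesis during the day (not counting the evening’s removal) to add compensation sheaths"), 1.b ("Did you have the fear at one (or more) moment(s) of the day, of losing your prosthesis") and 2.b ("Do you feel pistoning movement of your prosthesis when walking"). The last two are scored from 0 for not at all to 10 for a lot.

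**The concern.** A grading rule for individual patients has to separate nothing happened from something happened, and this one cannot. Its lowest grade begins at the value expected under no effect. Table 1 says that patient-by-patient analysis should tell responders, non-responders and aggravated patients apart, but the bands have words only for the first group.

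The consequence is practical. According to the section on ethics approval and dissemination, each participant receives a personalized statistical report, and the health authorities are notified of the results. For the four visit outcomes no other per-patient analysis is named, so the band is what the report would rest on.

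The second difficulty is direction. The verbal definition speaks of improvement, while the formula counts B values above A values. The two agree only where higher is better. The analyst is to be blinded to the hypothesis and to phase allocation, so direction should be written down and not left to inference.

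**Working it through.** **1. Design.** Four phases of at least 7 days in 50 days give C(50 − 28 + 3, 3) = C(25, 3) = 2300 schedules, and 1/2300 = 0.0004. Both figures match the article's power section.

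**2. No-effect value.** If A and B values have the same distribution, Pr(YB>YA) = Pr(YB<YA), so NAP = 0.5. The article's conversion to d, read as d = 3.464 × (1 − √((1 − NAP)/0.5)), gives d = 3.464 × (1 − 1) = 0 at NAP = 0.5.

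**3. Number of visit values.** Table 3 has two measurements per visit, before and after the prosthetist's action. A true switch gives one A and one B value. A placebo visit, used when a phase exceeds 14 days, adds two values to one condition. At most two phases can exceed 14 days, since three would need 3 × 15 + 7 = 52 days. ABAB contains three switches, giving a base of 3 v 3. The power section counts four true transitions; if the fourth is the change from connected acclimation to the first A phase, and it is measured, the base is 4 v 4. Both are shown.

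**4. Exact null distribution, assuming no ties and independent points.** At 3 v 3 the 20 orderings give 1, 1, 2, 3, 3, 3, 3, 2, 1, 1 for U = 0 to 9, with NAP = U/9. Then 10/20 = 50% exceed 0.5, 7/20 = 35% reach 6/9 = 0.67 or more, and 1/20 = 5% reach 1. The same enumeration for every schedule, with cuts midway between the printed bands (0.655 and 0.925), gives:

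| Schedules | Points, 3 switches | Moderate or large | Large | Points, 4 transitions | Moderate or large | Large |
|---|---|---|---|---|---|---|
| 84, no long phase | 3 v 3 | 35.0% | 5.0% | 4 v 4 | 24.3% | 2.9% |
| 1712, one long phase | 3 v 5 or 5 v 3 | 28.6% | 3.6% | 4 v 6 or 6 v 4 | 23.8% | 1.0% |
| 336, one long A and one long B | 5 v 5 | 21.0% | 0.8% | 6 v 6 | 19.7% | 0.4% |
| 168, two long of one kind | 3 v 7 or 7 v 3 | 25.8% | 1.7% | 4 v 8 or 8 v 4 | 23.0% | 0.8% |
| All 2300, weighted | | **27.5%** | **3.1%** | | **23.2%** | **0.9%** |

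Null patients at NAP ≥ 0.5, averaged over all schedules: 50.0% with three switches, 54.1% with four transitions.

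**5. Daily outcomes.** 8000 null patients were simulated per setting under this randomization, with the article's intra-patient variance of 2 and an assumed first-order autocorrelation of 0 to 0.8. NAP reached 0.5 in 49.6-51.1% of patients in every setting. Moderate or large labels occurred in 2-4% without autocorrelation and 14-21% at 0.8.

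**6. Direction.** Take a lower-is-better outcome with variance 2 that improves by 2 points (both figures are the article's, stated for comfort and borrowed here). The probability of improvement is Φ(2/√(2 + 2)) = Φ(1) = 0.84, while the printed formula taken literally gives 1 − 0.84 = 0.16. For 1 point: Φ(0.5) = 0.69 against 0.31.

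**The case against.** The strongest reply is that these labels decide nothing. NAP is a descriptive effect size on a published scale. Daily outcomes have a randomization test, and the group conclusion rests on a Bayesian posterior. Any signed effect size falls on the favourable side about half the time under no effect, so the 50% is not a type I error rate. All of that stands, and it limits the finding to secondary, patient-level labels. It does not rescue a rule that says an effect is present at the value where its own formula says there is none. Citing a source for the bands does not remove that conflict.

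A reader might infer that real gains on pistoning, fear of losing the prosthesis and sheath additions will be scored as losses. The documents do not support this. The sentence that prints the formula defines NAP as improvement, the objectives ask for a decrease in felt stump volume variation, and the formula can be read as the generic higher-is-better form. Gains become losses only if it is applied literally. The L-Test belongs in this list only if it is scored as time, which the article does not say.

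A reader might also take the 3 v 3 figures, 35% and 5%, as typical. That configuration arises in only 84 of 2300 schedules (3.7%), and only on the three-switch count.

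Finally, the absence of an interval or test for NAP may be detail left to an analysis plan. It is not raised as a fault here, only used in the remedy.

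**Conclusion.** The band rule is wrong as written: it starts at chance, calls chance an effect, and has no words for no effect or deterioration. On any one outcome, about half of patients with no effect would receive an effect label. On visit outcomes, 23-28% would be labelled moderate or large and 1-3% large. The visit figures assume untied and independent values, equally likely schedules, and two values at each switch or placebo visit; before-and-after values from one visit may well be correlated. The label of at least a small effect does not depend on few points, since daily data give the same half.

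Direction is a smaller defect. Formula and definition disagree for 1.a, 1.b and 2.b, and the text writes down no reversal.

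The weight falls on the four visit outcomes at patient level. The primary outcome's test and the group conclusion do not depend on the bands.

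**What to change.** - State that NAP = 0.5 means no effect and that values below 0.5 mean deterioration.
- List the direction of improvement for each outcome and compute NAP in that direction, reversing 1.a, 1.b and 2.b, and the L-Test if it is scored as time.
- Report each NAP with a confidence interval, and do not describe a single patient's visit-outcome NAP as an effect from the band alone. Moving the lower cut to 0.66 would not be enough, since the 23-28% above would remain.
- Base the conclusion on each visit outcome on NAP pooled over the 20 patients, with an interval that allows for clustering by patient.

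The cost is wording in the analysis text; no data collection changes. The downside is that few or no single patients will carry an effect label on visit outcomes. At 3 v 3 the smallest exact two-sided p is 2/20 = 0.10, so an exact 95% interval could never exclude 0.5. At 3 v 5 (2/56 = 0.036) or 4 v 4 (2/70 = 0.029) only complete separation reaches 0.05. An interval gate is therefore not a workable route to individual labels on these outcomes, which is why the conclusion should move to the pooled estimate.
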